### Data monitoring

A DMC will be established, which is independent of the trial sponsor and study investigators. The DMC will be composed by experts of the field related to the study
^36^ (at least 1 oncologist, 1 anesthesiologist, 1 psychiatrist, 1 pharmacologist, 1 patient advocacy, and 1 statistician). All members of the DMC will have to declare competing interests. Besides, the DMC will also monitor recruitment, inclusion rate, baseline characteristics, participant adherence, adverse events and safety monitoring every 15 days confidentially
^37^.

### Harms

Solicited and spontaneously reported adverse events will be collected by the outcome assessors at each planned visit for a clinical assessment. Details about efficacy and safety of the trial medication have been reported previously (see above).

### Sample size calculation

Sample size is based on practical and clinical considerations for this phase II trial. Based on a previous study (case series) assessing the analgesic effect of nasal esketamine
^38^ we obtained a standard deviation of 5.5 (that is the 75% upper limit of the confidence interval of the standard deviation). However, we would like to emphasize that power alone will not be relevant for the clinical interpretation of the study results, especially in a clinical trial
^39,
40^.

Considering the population of patients with refractory cancer pain (20%), to achieve a primary outcome reduction of 3 points on the 11 points NPRS with a power of 80% and an alpha error of 5%, a sample size of 108 subjects is needed. Based on previous studies in this patient population a dropout rate of 10% is estimated
^39,
41^, so for reasons of compensation, a total sample size of 120 participants will be recruited
^42,
43^.

### Statistical analysis plan

For the purpose of descriptive statistics all numerical continuous data will be presented as means or medians with standard deviation (SD) and interquartile ranges (IQR) respectively, as measures of dispersion. Categorical data will be presented in the form of proportions, frequencies or percentages. For all primary and secondary analysis, the intervention arm (nasal esketamine plus opioid therapy plus adjuvant standard analgesia) will be compared with the control group (placebo plus opioid therapy plus adjuvant standard therapy).

The P-values will be reported with two decimal points; all our tests will be 2-sided p-values with a level of significance of <0.05 to consider statistical significance. The statistical software to be employed is an up-to-date version of STATA (StataCorp LLC, College Station, Texas, USA), managed by professional blinded statisticians. After the analysis of all data, if the effect of esketamine doesn't last until next dose, a clustered analysis might be performed using results from all visits to evaluate acute efficacy of the drug against placebo.

***Missing data.*** According to our sample size calculation, we are considering an estimation of missing data of 10% of the participants, which may leave the study for several reasons that can include death secondary to cancer, adverse reactions, lack of improvement, early recovery, and others
^44,
45^.

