## Abstract

**Background:**  Cancer is the second leading cause of death globally. Up to 86% of advanced cancer patients experience significant pain, while 10-20% live in chronic pain. Besides, increasing prescription of opioids resulted in 33,000 deaths in the US in 2015. Both reduce patients’ functional status and quality of life. While cancer survival rates are increasing, therapeutic options for chronic opioid refractory pain are still limited. Esketamine is the s-enantiomer of ketamine, with superior analgesic effect and less psychotomimetic side effects. Intranasal esketamine was approved by the FDA for treatment-resistant depression. However, its use in chronic cancer pain has never been tested. Therefore, we propose a phase II, randomized, placebo-controlled trial to evaluate the efficacy and safety of intranasal esketamine in chronic opioid refractory cancer pain.

**Methods and analysis:** We will recruit 120 subjects with chronic opioid refractory pain, defined as pain lasting more than 3 months despite optimal therapy with high dose opioids (>60 mg morphine equivalent dose/day) and optimal adjuvant therapy. Subjects will be randomized into two groups: intranasal esketamine (56mg) and placebo. Treatment will be administered twice a week for four consecutive weeks. The primary outcome is defined as reduction in the Numeric Pain Rating Scale (NPRS) after first application. Secondary outcomes include NPRS reduction after four weeks, the number of daily morphine rescue doses, functional status and satisfaction, and depression.

**Conclusion:** This study may extend therapeutic options in patients with chronic pain, thus improving their quality of life and reducing opioid use.

**Trial registration:** Clinical Trials.gov,
NCT04666623. Registered on 14 December 2020

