### Objectives

This research aims to assess the efficacy and safety of a four-week treatment with intranasal esketamine (56 mg) twice a week, combined with opioid analgesic and adjuvant standard therapy in the management of adult patients with severe and opioid refractory chronic cancer pain.
****

The primary aim is to investigate the analgesic efficacy of intranasal esketamine as an add-on therapy to potentially improve opioid resistant pain in cancer patients. We will evaluate whether intranasal esketamine alleviates chronic pain in this population by assessing the reduction with the Numeric Pain Rating Scale (NPRS) after the first dose of esketamine compared to baseline
^18^.

Our secondary aims are:

1.Assessment of safety
^19^ of this novel treatment. This will be measured by a self-reported and questionnaire-guided adverse events report.2.Evaluation if esketamine treatment reduces the number of morphine rescues required daily by the patient.3.To compare the patients’ functional status between both treatment groups.4.To evaluate the response of depression score to esketamine therapy5.To analyze if there is a difference in the efficacy of esketamine depending on the type of cancer and depression disorder of the patient.6.To analyze the sustainability of the effect after each dose throughout the time of treatment.

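### Response-related departures are counted as expected missing data and met only by a larger sample, which leaves the four-week comparison open to bias that could be avoided

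*Protocol article*

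**What the plan says.** The Missing data paragraph takes its 10% from the sample size calculation and describes it as participants "which may leave the study for several reasons that can include death secondary to cancer, adverse reactions, lack of improvement, early recovery, and others". The Sample size calculation section answers this by recruiting 120 where 108 are needed. The article describes no other provision.

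The outcomes that depend on data after the first dose are these:

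- The Abstract: "Secondary outcomes include NPRS reduction after four weeks, the number of daily morphine rescue doses, functional status and satisfaction, and depression".
- Objectives, secondary aim 6: "To analyze the sustainability of the effect after each dose throughout the time of treatment". The Secondary outcomes text describes this as the pattern of NPRS after each dose.
- Trial design, which gives the primary endpoint as NPRS change at weeks 0 to 4. The Abstract, Objectives and Outcomes sections instead place the primary outcome after the first dose.

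On collection, NPRS and PHQ-9 are taken at enrolment and at each visit, dosing is twice weekly for four weeks at the facility, and the weekly clinical evaluation is described for the treatment period. Rescue morphine is recorded by mobile application or personal diary. The Blinding section mentions discontinuation of study drug once, in connection with code breaks, and does not say what follow-up then applies.

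**The concern.** Apart from death, the named reasons are ones for which a participant might stop the spray. None of them prevents pain from being measured afterwards. Lack of improvement and early recovery are values of the outcome, so if those participants go unmeasured at week 4, whether a value is missing depends on what it would have been. The reasons may also differ by arm, for example adverse reactions on esketamine and lack of improvement on placebo. Participants still observed at week 4 would then no longer be comparable as randomized.

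Recruiting more participants does not help, because the extra ones are subject to the same selection. A later analysis can model or bound the missing values but cannot recover measurements that were never taken. Whether they are taken is settled by the visit schedule, the consent form and the case report form.

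**Working it through.** **Inputs from the article.** Difference: "to achieve a primary outcome reduction of 3 points on the 11 points NPRS". SD: "we obtained a standard deviation of 5.5". Error rates: "with a power of 80% and an alpha error of 5%, a sample size of 108 subjects is needed". Sidedness: "all our tests will be 2-sided p-values with a level of significance of <0.05". Arms: "Subjects will be randomized into two groups: intranasal esketamine (56mg) and placebo"; the ratio is not given, so 1:1 is assumed. Loss: 10%.

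**1. The plan's own figure.** Normal approximation per arm: 2 × (1.960 + 0.842)² × (5.5/3)² = 52.8, so 53 per arm and 106 in total. The two-sample t-test gives 53.74, so 54 per arm and 108 in total, which matches. Allowing for loss: 108 / (1 − 0.10) = 120, which also matches. The planned loss is therefore 12 of 120. The inflation protects power only: t-test power is 80.2% with 54 per arm observed and 84.2% with all 60.

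**2. Bias from analysing only those still observed.** In each arm let p be the share lost and g the mean change in leavers minus the mean change in stayers. The all-participant mean equals the stayers' mean plus p × g. Hence:

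observed difference − all-participant difference = −(p_E × g_E − p_P × g_P), where E is esketamine and P is placebo.

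The sample size does not appear in this expression.

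**3. Illustrations.** Each loses 12 in total, and all response values are assumptions.

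- *Balanced and alike:* 6 of 60 lost in each arm with the same g. The bias is 0.
- *(a) Opposite reasons, 6 of 60 in each arm:* esketamine stayers −3 and early-recovery leavers −5; placebo stayers −1.5 and non-improving leavers 0. Esketamine: 0.9 × (−3) + 0.1 × (−5) = −3.20. Placebo: 0.9 × (−1.5) + 0.1 × 0 = −1.35. The all-participant difference is −1.85 and the difference among stayers is −1.50, so the effect is understated by 0.35.
- *(b) Unequal loss, 9 of 60 against 3 of 60:* leavers 0 in both arms, stayers −3 on esketamine and −1 on placebo. Esketamine: 0.85 × (−3) = −2.55. Placebo: 0.95 × (−1) = −0.95. The all-participant difference is −1.60 and the difference among stayers is −2.00, so the effect is overstated by 0.40.

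**4. Range.** For leaver–stayer gaps of equal size in both arms, from 1 to 5.5 points (assumed):

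| Loss pattern | Bias in points |
|---|---|
| 6/6, same direction | 0 |
| 9/3, same direction | 0.10 to 0.55 |
| 12/0, or opposite directions in the two arms | 0.20 to 1.10 |

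**5. Scale.** The shifts of 0.35 and 0.40 are 0.35/3 = 12% and 0.40/3 = 13% of the 3-point design difference, which was set for the primary outcome. The standard error with 54 per arm is 5.5 × √(2/54) = 1.06, so they are roughly a third of a standard error (0.33 and 0.38). If a bias ran towards the null against a true difference of 3 with SD 5.5, power would fall from 80% to about 75% (bias 0.2), 61% (0.6) or 43% (1.1).

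**The case against.** The strongest reply is that the sentence is a forecast. It says why some people may go, in order to explain a planning allowance, and participants do leave trials because they feel no better or because they feel well. A reader might infer that everyone who stops the spray is withdrawn and supplies nothing further. The article does not say so: no section states that stopping drug ends follow-up, and rescue use is recorded by app or diary, independently of dosing visits. The full protocol may already provide for continued collection.

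A reader might also infer that the four-week results are lost in the very patients who determine them. That is too strong. About 12 of 120 are expected to leave for all reasons, including death from cancer, about 90% still contribute, and leavers keep their data up to departure. Nor is the primary outcome broadly compromised: a change after the first dose is observed before almost any such departure.

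On size, every response value above is assumed, both worked cases treat all leavers as response-related, and they point in opposite directions. The after-each-dose sustainability outcome cannot be filled from people no longer being dosed.

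All of this stands, and it narrows the point. It leaves one thing unanswered: the article itself names response-related departure as its expected missing data, and its only stated provision cannot address bias.

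**Conclusion.** The point holds in limited form. As written, response-related departures are accepted as missing data and met only by the increase from 108 to 120. This plausibly makes the missingness informative for the secondary four-week NPRS, BPI and PHQ-9 comparisons, and for the primary endpoint only if the week 0 to 4 version under Trial design governs.

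The size and direction of any bias cannot be established from the article. It is zero when losses are balanced and alike, 0.35 to 0.40 points in either direction in the two worked cases, and at most about 1.1 points over the assumed gaps. These figures rest on 1:1 allocation, a 10% total loss, every loss being response-related, an analysis of observed participants only, and assumed responses. They show that the issue is not negligible; they do not predict a bias. The change is worth making before recruitment because it is cheap and cannot be made up for at the analysis stage.

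**What to change.** In the Missing data and Outcomes sections, distinguish stopping study drug from leaving the study. State that participants who stop dosing for any reason remain in follow-up, with weekly NPRS, BPI, PHQ-9 and rescue use collected to week 4 by telephone or the planned app or diary. Only death or withdrawal of consent to data collection ends follow-up. Include these values in the four-week between-arm comparison, and keep the after-each-dose sustainability analysis to doses actually given. No dosing or treatment-stopping rule changes, and 108 and 120 stand.

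The cost is a short protocol passage, a line in the consent form and a few contacts for about 12 participants over at most four weeks. The Study status section says recruitment has not begun, and the Protocol amendments section gives the route. The downside is minor staff time and some dilution of a purely on-treatment effect by off-drug values.

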## Ethical considerations

### Research ethics approval

Research ethics committee/institutional review board (REC/IRB) approval will be obtained by the local ethics committee or institutional review board of the site center prior to begin of recruitment.

### Protocol amendments

Protocol amendments, if any, should be registered and approved by the local ethics committee. Accordingly, study protocol and if applicable informed consent form will be adjusted and investigators involved in the trial informed immediately.

## Dissemination

After completion of data acquisition and analysis, the results will be summarized and published. Accordingly, patients will be informed about allocation and trial results via telephone calls and optional visit in person. Manuscript writing will be performed by the investigators and there will be no public access granted to the raw data.

### Confidentiality

Personal information about enrolled patients will be collected by study nurses of the study site. Collected information will be saved in coded folders and investigators, outcome assessors and statisticians will receive a pseudononymized version of the data. The data and information will be stored at a previously defined location after completion of the trial for 5 additional years.

### Access to data

Only investigators and statisticians will have access to the final version of the data. To secure restricted access to the data, corresponding files will be coded.

### Ancillary and post-trial care

Meanwhile and after completion of the trial patients will be treated according to current guidelines and standards of care. Any harm associated with the participation of the trial is not expected as patients continue to receive standard of care.

## Study status

Not yet recruiting.

## Data availability

### Underlying data

No data is associated with this article.

### Reporting guidelines

Figshare: SPIRIT and TIDieR checklist for ‘IMPORTANCE trial: a provisional study-design of a single-center, phase II, double-blinded, placebo-controlled, randomized, 4-week study to compare the efficacy and safety of intranasal esketamine in chronic opioid refractory pain’,
https://doi.org/10.6084/m9.figshare.13435742.v2
^46^.

Data are available under the terms of the
Creative Commons Zero "No rights reserved" data waiver (CC0 1.0 Public domain dedication).
